## Abstract

**Background:**

Myalgic encephalomyelitis/chronic fatigue syndrome (ME/CFS) is a serious illness of biological origin characterized by profound physical and cognitive exhaustion and postexertion malaise. Pacing is a common strategy used to manage available energy and complete activities of daily living; yet little research has investigated this as a strategy to increase physical activity levels. Typically, people living with ME/CFS are faced by unique barriers to physical activity participation and are less physically active than healthy peers. As such they are at increased risk of physical inactivity–related health consequences. Active video games may be a feasible and acceptable avenue to deliver physical activity intervention by overcoming many of the reported barriers to participation.

**Objective:**

The primary objective of this pilot study is to determine the feasibility and acceptability of active video games to increase physical activity levels of people with ME/CFS. The secondary aims are to explore the preliminary effectiveness of pacing and active video gaming to pacing alone and pacing plus conventional physical activity to increase the physical activity levels of adults with ME/CFS and explore the relationship between physical activity and cumulative inflammatory load (allostatic load).

**Methods:**

This study will use a mixed method design, with a 3-arm pilot randomized controlled trial, exit interviews, and collection of feasibility and process data. A total of 30 adults with ME/CFS will be randomized to receive either (1) pacing, (2) pacing and conventional physical activity, or (3) pacing and active video gaming. The intervention duration will be 6 months, and participants will be followed up for 6 months postintervention completion. The intervention will be conducted in the participant’s home, and activity intensity will be determined by continuously monitored heart rate and ratings of perceived exertion. Feasibility and acceptability and process data will be collected during and at the end of the intervention. Health-related outcomes (eg, physical activity, blood samples, quality of life, and functioning) will be collected at baseline, end of intervention, and 6 months after intervention completion.

**Results:**

This protocol was developed after 6 months of extensive stakeholder and community consultation. Enrollment began in January 2017; as of publication, 12 participants were enrolled. Baseline testing is scheduled to commence in mid-2017.

**Conclusions:**

This pilot study will provide essential feasibility and acceptability data which will guide the use of active video games for people with ME/CFS to increase their physical activity levels. Physical activity promotion in this clinical population has been poorly and under-researched, and any exploration of alternative physical activity options for this population is much needed.

**Trial Registration:**

Australia New Zealand Clinical Trials Registry: ACTRN12616000285459; https://www.anzctr.org.au/Trial/Registration/TrialReview.aspx?id=370224 (Archived by WebCite at http://www.webcitation.org/6qgOLhWWf)

## Introduction

Myalgic encephalomyelitis/chronic fatigue syndrome (ME/CFS) is a complex, serious illness of biomedical origin characterized by profound physical and cognitive exhaustion and postexertion malaise [1]. Symptoms such as fatigue and cognitive impairments are typically made worse to the point of collapse after physical exertion [1]. The combination of physical inability to be active due to the condition and behaviors to avoid potential flare-up results in people with ME/CFS being less physically active than healthy controls [2].

The mechanisms underlying ME/CFS remain unclear, and studies report associations with multiple individual proinflammatory markers and indicators of immune activity, but the findings are inconsistent [3]. A potential mechanism by which physical activity plays a role in managing chronic conditions is through allostasis: the body’s response to stress orchestrated by the hypothalamic-pituitary-adrenal axis and the central nervous system via the production of stress hormones [4]. The detrimental negative effect of allostasis can be quantified as allostatic load (AL). The theoretical mechanism between AL and physical activity has recently been empirically supported, with higher levels of physical activity associated with lower AL in Mexican American adults [5] and middle-aged women [6]. Further, adults living with ME/CFS are reported to have higher AL than healthy controls [7,8]. It is widely accepted that cumulative biomarkers are stronger predictors of morbidity and mortality, yet recent research into ME/CFS continues to investigate individual neuroendocrine and immune biomarkers with limited success and inconsistent findings [3]. Further, few AL studies are longitudinal or interventional in nature, limiting the relationships and conclusions that can be drawn.

Physical activity is essential for health and well-being and has a role in prevention and management of muscle atrophy and many chronic conditions such as cardiovascular disease, osteoporosis, and some cancers [9]. There is much debate in the literature surrounding the effectiveness and safety of exercise or physical activity-based interventions for people with ME/CFS. In this population, the majority of physical activity–based interventions have employed a Graded Exercise Therapy (GET) approach. Typically, after setting baseline levels, the intention of GET protocols is to incrementally increase activity despite possible changes in symptom severity. One common criticism of GET protocols is they typically suggest stabilization of activity progression at the point of symptom flare-up but do not appear to include modification or cessation of activity to promote symptom resolution. The results of GET protocols are mixed, with some reporting symptom improvement [10,11]. The risk of adverse responses to GET is not clear from intervention studies; however, support group surveys of people living with ME/CFS suggest a significant proportion of these interventions result in negative experiences during the intervention [12].

An alternative approach to delivery of physical activity interventions is pacing. Pacing is a typical strategy used by people with ME/CFS to manage their activities of daily living within their available energy envelope by structuring and organizing their daily activities. Pacing is typically well accepted by people living with ME/CFS (according to patient surveys) and is used primarily to manage symptom flare-ups and work within the available energy, but it is also recommended that pacing can help to slowly increase the energy envelope and thus the level of activity performed. Pacing is a flexible, symptom-contingent process that can be used to increase physical activity levels. Survey data suggests a greater percent of people living with ME/CFS feel pacing improved their symptoms (45%, n=69) compared to GET (12%, n=77) [12]. In addition, anecdotal evidence suggests a large percentage of people living with ME/CFS already use pacing and heart rate (HR) monitoring to some extent (personal communication by ME/CFS Australia [SA] spokesperson, March 2016), and as such, pacing will be considered the control situation for this study.

Only one published study can be located that has employed a flexible symptom-contingent protocol (ie, pacing using HR and perceived exertion monitoring) to increase activity levels in people with ME/CFS [13]. The study demonstrated improvements in physiological outcomes (eg, blood pressure, cognitive ability) but no change in physical activity between the groups postintervention. The study used a self-report activity questionnaire with poor reliability at low intensity levels of activity, which is concerning because this accounts for almost all physical activity in most people with or without ME/CFS, and only low to moderate validity with other self-reported physical activity outcomes [14]. Overall, the flexible, symptom-contingent approach to increasing activity levels in people with ME/CFS has not been adequately researched. An important finding from the Wallman et al [13] study is that none of the participants in the exercise group rated themselves as any worse and 91% rated themselves some degree better overall. The current study will build on this small body of literature by investigating pacing alone versus pacing and physical activity using objective measures of physical activity and safely monitoring activity intensity via continuous HR monitoring and ratings of perceived exertion (RPE).

People with ME/CFS report unique barriers to participation in physical activity. These barriers include extreme fatigue just getting to and from structured activity, greater difficulty being active standing compared to sitting, and ability to participate in only very short durations of activity [1]. Interventions using commercially available active video games, such as Xbox Kinect, can overcome many of these barriers for people with ME/CFS. Active video games can be played at home either while standing or seated, can be easily played for short periods of time (eg, 1-2 minutes), and provide choice of different gaming activities—factors which will potentially reduce patient dissatisfaction and drop out [15].

An inability to fully participate in their family’s lives and community often results in people living with ME/CFS reporting depression, social isolation, and lack of connectedness [1]. Active video games have the potential to provide an avenue for family connectedness and promote a feeling of normality while enabling participation (potentially with others) in an everyday activity. People’s experiences with active video gaming suggest substantial benefits including feelings of empowerment, reductions in depression, increased psychosocial well-being, and increased social connectedness by playing with family members [16].

Active video gaming has been shown to be feasible and acceptable to other chronic health populations such as those with cerebral palsy and stroke and is commonly played while sitting in these populations [17]. Evidence suggests active video gaming can improve a range of rehabilitative outcomes, increase physical activity levels among sedentary and frail elderly adults, and increase cognitive performance and reduce fatigue in women with systemic lupus erythematosus [18,19,20]. Despite the evidence to suggest active video gaming as effective and relevant, no studies have investigated the feasibility or acceptability of active video gaming in adults with ME/CFS.

The primary objective of this pilot study is to investigate the feasibility and acceptability of pacing and active video gaming to increase the physical activity levels of adults with ME/CFS.

The secondary objectives of this study are to (1) explore the preliminary effectiveness of pacing and active video gaming to pacing alone and pacing and conventional physical activity to increase the physical activity levels of adults with ME/CFS and (2) explore the relationship between allostatic load and physical activity in people with ME/CFS.

The related hypotheses are (1) preliminary evidence of benefit from pacing and active video gaming to increase physical activity compared to pacing alone will be demonstrated, (2) preliminary evidence of equal benefit of pacing and video gaming to increase physical activity levels compared to pacing and conventional exercise will be demonstrated, and (3) preliminary evidence of a negative relationship will be demonstrated between allostatic load and physical activity.

## Methods

### Trial Design

A mixed-method study will be conducted comprising an exploratory 3-armed randomized controlled pilot study (1:1:1 allocation ratio) of pacing versus pacing and conventional physical activity versus pacing and active video gaming; qualitative exit interviews and collection of process data to investigate the feasibility and acceptability of the approach. The study protocol has been approved by the University of South Australia Human Research Ethics Committee (protocol 0000035299). The protocol is registered with the Australia New Zealand Clinical Trials Registry [ACTRN12616000285459]. All participants will be required to provide written informed consent prior to enrolling in the study and report general practitioner consent to participate.

### Protocol Development

A stakeholder advisory group was convened including 2 representatives from the local state ME/CFS society, a rheumatologist with extensive clinical and research knowledge of ME/CFS, a general physician with extensive clinical expertise in managing ME/CFS, 2 adults currently living with ME/CFS, and the research team. The primary purpose of the stakeholder advisory group was to assist in the consumer-driven and evidence-based development of the final protocol. A 6-month consultative development phase was completed in December 2016. The stakeholder advisory group welcomed and considered comments and concerns from external bodies (eg, national and international support groups).

### Intervention

After baseline assessment, participants will be block randomized (block size = 6, 1:1:1 allocation ratio) into pacing only, pacing plus conventional physical activity, or pacing plus active video gaming (Figure 1).

Participants will be randomized using a computer-generated random number sequence and opaque sealed envelopes generated by a University of South Australia researcher not involved in the study. All participants will receive telephone support from the research assistant once a week for the first 3 months of the intervention and every 2 weeks for the last 3 months of the intervention, and participants can contact the research assistant at any additional time. At the end of the 12 months, participants still enrolled will be provided with an Xbox Kinect unit in acknowledgement of their participation.

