### Adverse Events

A comprehensive adverse events reporting protocol has been developed for this study based on the stakeholder group feedback and previous literature. An adverse event (AE) will be defined as “any clinical change, disease, or disorder experienced by the participant during their participation in the trial, whether or not considered related to the intervention studied in the trial.”

AE data will collected (1) during every preplanned phone contact between the participant and the research assistant, (2) if the participant contacts the research assistant to report an AE, and (3) during the 3 testing sessions (baseline, 6 months, and 12 months). Questions will be asked about the following 3 categories to encourage the participant to report AEs: any new comorbid medical conditions reported if not previously reported at baseline, any events for which the participant consulted their general practitioner or other medical advisor or took medication, any other events that might have affected the health status of the participant (eg, increased work stress).

The research assistant will have knowledge of participant allocation (ie, control or active intervention group) and as such will be able to use any AE data reported to provide activity counseling and advice regarding the intervention. If an AE is reported, participants will be asked whether they consider the event to be directly caused by the intervention.

A serious adverse event (SAE) will be defined as one of the following outcomes:

DeathThreat to life (ie, an immediate, not hypothetical, risk of death at the time of the event)Required hospitalization except for elective treatment of a preexisting conditionIncreased severity and persistent disability, defined as (1) severe (ie, significant) deterioration in the participant’s ability to carry out their important activities of daily living (eg, employed person no longer able to work, caregiver no longer able to give care, ambulant participant becoming bed bound) and (2) symptom and disability persistent (ie, of at least 4 weeks continuous duration)Any other important medical condition which, though not included in the above, might require medical or surgical intervention to prevent one of the outcomes listed

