## Results

A 6-month extensive consultative protocol development phase has been completed; 3 comprehensive rounds of protocol topics, comments, and plans for amendment occurred.

The first round focused on the following general topics: inclusion criteria, time frame between effort testing and intervention commencement, time and frequency of assessment, and the inclusion of continuous HR data collection. The Karnofsky Scale and alternative disability scales were discussed. The second round included discussion on the following broad topics: design modification to 3-arm trial, symptom history data collection, and the pacing and physical activity protocol. The third round involved discussion on the following topics: AEs protocol, adherence diary, and clarification of maximal and submaximal effort test procedures.

Virtual meetings allowed for interactive group discussion, and consensus was reached on all aspects of the protocol. All members of the stakeholder advisory group have endorsed the current protocol. Enrollment began in January 2017; as of publication, 12 participants were enrolled. Baseline testing is scheduled to commence in mid-2017.

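### A single published block size of 6 in an unblinded, single-campus trial makes about one allocation in five knowable in advance; varied, undisclosed block sizes would reduce this at almost no cost

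*Protocol article*

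**What the plan says.** The Trial Design section describes an "exploratory 3-armed randomized controlled pilot study (1:1:1 allocation ratio"), and the abstract's Methods paragraph sets the size: "A total of 30 adults with ME/CFS will be randomized". The Intervention section states that after baseline assessment "participants will be block randomized (block size = 6, 1:1:1 allocation ratio"). It gives no other block size and no stratification. The sequence is computer-generated and held in "opaque sealed envelopes generated by a University of South Australia researcher not involved in the study".

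Three other places bear on who can see the sequence unfold:

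- **Setting:** testing is at one university campus, and home visits teach the allocated condition and install the games where they apply.
- **Intervention:** "All participants will receive telephone support from the research assistant once a week for the first 3 months of the intervention", so one role is in contact with all three arms.
- **Adverse Events:** "The research assistant will have knowledge of participant allocation (ie, control or active intervention group").

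The Results section adds that "as of publication, 12 participants were enrolled", with baseline testing still to start in mid-2017. The article does not say who decides the order in which participants are randomized, who opens the envelopes, or whether that person is kept from past allocations.

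**The concern.** Concealment has two parts: the next card must not be seen, and it must not be deducible. Opaque envelopes prepared by an outsider deal with the first. A block of one known size weakens the second, because each block must close with exactly two places per arm. Someone who has seen the earlier assignments in a block can subtract them from 2/2/2 and read off what remains.

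At stake is who enters which arm. The Sample Size section rests the gaming feasibility and acceptability data on 10 participants, and the Feasibility and Acceptability section holds exit interviews with the gaming arm only. One participant is therefore a tenth of that evidence. If knowledge of the next allocation influenced who was randomized next, the make-up of the gaming arm could shift, and with it the exploratory activity comparison. That the trial is not powered does not answer this, because selection bias is a separate matter from power.

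**Working it through.** The article states no predictability figure, so there is none to reproduce.

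**Inputs**
- Block of 6, 1:1:1, so 2 places per arm (Intervention).
- Three arms (Trial Design).
- 30 participants (abstract, Methods), so 30/6 = 5 complete blocks.
- Assumption: the observer knows the block size and has followed every earlier allocation in order.

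**Allocations known for certain.** An allocation is certain when every remaining place in the block belongs to one arm.
- Places 1 to 4: never, since at least three places remain and no arm has more than two.
- Place 5: certain when the last two places are the same arm. Given the arm in place 6, one of the five other places holds its partner, so the probability is 1/5.
- Place 6: always certain.
- Per block: 1/5 + 1 = 1.2. As a share: 1.2/6 = 20%. Over five blocks: 5 × 1.2 = 6 of 30, and never fewer than 5. Enumerating all 90 distinct orders of a 2/2/2 block gives the same 20%.

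**Best guess (always name the arm with most places left)**

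| Place | Probability of a correct guess |
|---|---|
| 1 | 1/3 |
| 2 | 2/5 |
| 3 | 1/2 |
| 4 | (2/5)(1/3) + (3/5)(2/3) = 8/15 |
| 5 | (1/5)(1) + (4/5)(1/2) = 3/5 |
| 6 | 1 |

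The sum is 101/30 = 3.37 per block, and 3.37/6 = 56.1%, against 33.3% by chance.

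**At least one arm ruled out.** The probabilities at places 3 to 6 are 1/5, 3/5, 1 and 1. They sum to 2.8, and 2.8/6 = 46.7%, or 14 of 30.

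**With varied block sizes.** Two blocks of 6 and two of 9 total 12 + 18 = 30, with 2×2 + 2×3 = 10 per arm. The rows for varied sizes come from simulation over 30 allocations, with an observer who updates on everything seen so far.

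| List | Certain | Best guess |
|---|---|---|
| Fixed 6 (as stated) | 20% | 56% |
| Two 6s and two 9s, composition unknown to the observer | about 5% | about 53–54% |
| Two 6s and two 9s, composition known, order unknown | about 9% | about 54% |

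In the last row the 30th allocation is always certain, because the totals are fixed at 10 per arm.

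**The case against.** The strongest case against is that no mechanism for steering is described. The statement that the research assistant knows allocations stands in the Adverse Events section and concerns counseling after allocation. Nowhere is that role said to enroll, schedule, order participants or open envelopes. The article also describes real safeguards: randomization after baseline assessment, a computer-generated sequence, and opaque envelopes from an uninvolved researcher. Details of envelope handling are commonly left to a full protocol, which is not shown.

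A reader might infer from the 12 people enrolled before baseline testing that staff had a queue from which to choose who is randomized next. The article does not say this. It reports only that they were enrolled and that testing had not begun. A reader might also infer that concealment is lost altogether. That is too strong: 80% of allocations are not certain, and one of the certain ones is the 30th, when no other enrolled participant remains to exchange.

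The benefit of the change is also limited. Best-guess success falls only from 56% to about 53–54%, and acceptability is drawn from interviews in one arm, not from a between-arm contrast.

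These points remove any claim that allocation is being steered and bring down the importance of the point. They do not remove the point itself. The fixed block size is a stated rule and not an omitted detail, the envelopes do not prevent inference from earlier allocations, and the composition of the gaming arm still matters when only that arm is interviewed.

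**Conclusion.** The point holds as an avoidable vulnerability to selection bias. With the stated block of 6, an observer who follows allocations in order knows 20% of them in advance (expected 6 of 30, at least 5) and guesses 56% correctly against 33% by chance.

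This rests on three assumptions: a single unstratified sequence, as the text describes; an observer who knows the published size; and complete knowledge of earlier allocations in order. Harm would also require that person to influence who is randomized next, which the article neither states nor excludes. The documents give no evidence of steering and no basis for putting a number on its effect on adherence, acceptability or activity.

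The change is worth making because it costs so little and, at publication, was still possible: randomization follows baseline assessment, and baseline testing had not started.

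**What to change.** Before the first randomization:

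1. Have the independent researcher regenerate the list with block sizes in random order, for example two blocks of 6 and two of 9 (total 30, 10 per arm).
2. Withhold both the sizes and the composition, until recruitment ends, from everyone who enrolls, schedules or delivers the intervention. This matters to the result: certain allocations are about 5% if the composition is unknown but about 9% if it is known. Any interim description should say only that block sizes vary.
3. Write the participant number on each envelope before it is opened.

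The work is minutes for the independent researcher. The downside is slightly looser balance part-way through recruitment: within a block of 9 two arms can differ by up to 3, against 2 within a block of 6. Final balance of 10 per arm is kept if all 30 are randomized. The change mainly removes certain knowledge; most of the guessing advantage over chance remains.
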